## Introduction

### Background

Severe obesity (class II and III; BMI ≥35 kg/m^2^) affects approximately 9.5% of Canadians [1]. Metabolic and bariatric surgery (MBS) is generally effective in inducing significant and lasting weight loss [2] while reducing the costs related to severe obesity and associated complications [3,4]. MBS offers significant health benefits and improves the quality of life [4,5]. The number of procedures performed worldwide has increased during the last decade in particular, reaching almost 700,000 surgeries performed in 2018 [6]. However, approximately half of the patients who have undergone MBS regain at least 10% and 20% of their maximum weight loss 1 year and 5 years after reaching their nadir weight, respectively [7].

In the context of MBS, physical activity (PA) is recommended given its multiple benefits [8,9]. Studies have shown that pre- and post-MBS PA can improve physical fitness, cardiometabolic health, quality of life, and depressive symptoms [10-17]. However, 70% to 95% of adults are inactive before MBS and remain so after MBS [18,19]. Thus, there is a need to develop interventions with the aim of increasing pre- and post-MBS PA. Introducing PA behavior change interventions before MBS with additional support offered after MBS seems to be an ideal approach to optimize MBS benefits and provide transitional support toward post-MBS lifestyle [20]. The most compelling evidence to support this assertion comes from studies that have shown that PA interventions delivered before MBS can increase PA until 1 year after MBS [21,22]. Furthermore, pre-MBS PA can improve physical fitness, which may help reduce perioperative complications and length of hospital stay [23]. Finally, participants’ motivation and readiness for PA increased close to their surgical date [24].

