### Statistical Analyses

Descriptive statistics will be computed for baseline sociodemographic, clinical, feasibility, and acceptability data derived from the numerical responses and close-ended questions.

All statistical analyses will be carried out using R and the following packages: scan, SCRT [112], metafor, ggplot2, and tydiverse. For the primary outcomes of a future large-scale trial, a comparison of daily MVPA based on accelerometer data between phases A1 and B1 will be carried out using a randomization test for a single-case experimental design [113] for each participant. Subsequently, individual effect sizes will be aggregated in a meta-analysis to obtain a group-based effect size. This will provide the necessary information for computing the required sample size for a future large-scale trial. A sensitivity analysis will also be performed to compare A1 and B1 using a Tau-*U* test [114]. Then, a second meta-analysis will be performed using the same approach. The global effect of the intervention on daily MVPA will be tested using another set of randomization tests comparing the ABABA phases. This test makes it possible to compare 2 short time series and to provide an effect size in case of a significant difference. This analysis will be performed on an individual scale.

Generalization measures (secondary outcomes for a future large-scale trial: health-related quality of life, anxiety, and depression symptoms) will be analyzed using the Reliable Change Index or cutoff score for descriptive purposes; the differences in individual scores across phases will be compared [115].

Theoretical construct measures (secondary outcomes for a future large-scale trial: PA enjoyment, motivational regulations for PA, basic psychological needs satisfaction and frustration, self-efficacy to overcome PA barriers, and social support for exercise) and self-reported MVPA will be analyzed using visual analysis. As recommended [116], stability, mean level change, and range of data by phase will be examined.

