## Discussion

### Principal Findings

Increasing MVPA uptake and maintenance in adults undergoing MBS is a public health priority. This study will provide critical evidence pertaining to the feasibility and acceptability of the TELE-BariACTIV aimed at promoting MVPA before and after MBS while addressing several barriers to MVPA and intervention engagement previously identified, as well as the protocol or methods proposed to evaluate it. The data collected in the individual interviews will help optimize the intervention and protocol or methods for a larger study. In addition, an estimate of the effect of the TELE-BariACTIV intervention on MVPA will be useful for calculating the required sample size for future multicenter large-scale trials.

This paper describes the protocol and intervention used in the TELE-BariACTIV study. To our knowledge, only 2 studies investigating PA behavior change interventions among adults undergoing MBS have been published [72,73]. The TELE-BariACTIV study extends these previous works by prolonging the duration of the intervention (to cover both before and after MBS) and accordingly integrates longer follow-up assessments to assess initial changes in PA and maintenance of PA. Furthermore, the intervention and protocol or methods were designed to be as accessible and simple as possible (ie, distance-based), with no need for in-person assessments or intervention sessions while still using an objective PA measure.

A single-case experimental study with multiple base levels (ABAB’A) design, in which a small group of participants is used to test causal relationships between variables of interest, is often used in behavior research because it allows rigorous experimental manipulation of independent variables and repeated measures of dependent variables over time [119]. This design has been used with various clinical populations to study different behaviors, including PA [87,120,121] in patients who have undergone MBS [122]. In addition, observational phases improve internal validity by controlling for maturation and historical variables, thus performing a function similar to that of the control group without intervention [75].

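### The pooled A1–B1 single-case effect size does not by itself supply what is needed to size the future large-scale trial, and it is only weakly controlled for time

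*Protocol article*

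**What the plan says.** The second objective (Objectives) is to estimate the effect of the intervention on presurgical MVPA so that a multicenter large-scale trial can be sized. The route is in Statistical Analyses:

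- For each participant, "a comparison of daily MVPA based on accelerometer data between phases A1 and B1 will be carried out using a randomization test".
- Then "individual effect sizes will be aggregated in a meta-analysis to obtain a group-based effect size", followed directly by the claim "This will provide the necessary information for computing the required sample size for a future large-scale trial".
- After that claim comes the secondary route: "A sensitivity analysis will also be performed to compare A1 and B1 using a Tau-*U* test". "Then, a second meta-analysis will be performed using the same approach".

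The section on MVPA as the future primary outcome says that the effect sizes for this purpose use data gathered immediately after B1. Principal Findings describes the observational phases as "thus performing a function similar to that of the control group without intervention".

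The article names no effect-size metric. It does not list a between-person SD of MVPA, or of its change, among the outputs, and it does not state the design of the future trial.

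**The concern.** There are two separate difficulties with calling the pooled value sufficient.

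**Scale.** A trial comparing groups of people is sized on a difference in min/day and on how much people differ from each other in MVPA or in its change. A standardized single-case effect divides by one person's day-to-day SD, which is a different quantity. Tau-U is a non-overlap index bounded by -1 and 1 and carries no unit at all.

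**Time.** The A1-to-post-B1 change contains whatever else changes over those weeks: time trend, reaction to being monitored, and regression to the mean after entry on low self-reported MVPA. The sentence likening the A phases to a control group suggests that these are removed.

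Sizing the next trial is the purpose of Objective 2. If the pooled value were used as stated, that trial could be far too small or needlessly large.

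**Working it through.** The article gives no future N, power, alpha, SD or effect size, so there is no figure to reproduce. Every SD and effect below is an assumption for illustration. Two-sided 5% alpha, 80% power and two equal arms are also assumed.

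**1. Scale of a standardized effect.** n per arm = 2(1.96 + 0.8416)² / d² = 15.70 / d². Take a true difference of 8 min/day. The between-person SD here is the SD of people's observed mean MVPA.

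| Daily SD within person | SD between persons | d on daily SD | n per arm from it | d on between-person SD | n per arm needed |
|---|---|---|---|---|---|
| 10 | 15 | 0.80 | 24.5 (25) | 0.533 | 55.2 (about 55) |
| 20 | 10 | 0.40 | 98.1 (about 98) | 0.80 | 24.5 (25) |

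The ratio of needed to computed n is (between SD / within SD)²: 2.25 in the first row and 0.25 in the second.

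If the between-person SD instead means the true person-level SD, noise left in a 7-day mean must be added: SD = √(between² + within²/7).

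- First row: √(225 + 14.3) = 15.5, so n = 15.70 × 239.3/64 = 58.7. The ratio is 58.7/24.5 = 2.4.
- Second row: √(100 + 57.1) = 12.5, so n = 15.70 × 157.1/64 = 38.5. The error is 98.1/38.5 = 2.5-fold.

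A wider assumed grid (change 10 min/day, daily SD 8 to 20, person-level SD 5 to 20) gives 11 per arm where 65 are needed at one extreme and 63 where 13 are needed at the other. In between, the two can agree by chance: with a daily SD of 16 and a person-level SD of 15 they are 41 and 42. The article contains nothing that says which case applies.

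**2. Tau-U.** Average non-overlap without trend correction was simulated for 12 people with 7 + 7 days and a person-level SD of 15. Changes of 5, 10 and 15 min/day with daily SDs of 6, 12 and 18 all have d = 0.83 and mean Tau of about 0.44. The sizes needed, 15.70 × (225 + within²/7) / change², are 145, 39 and 19 per arm. One value of Tau is therefore compatible with very different trials.

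**3. Control for time.** The schedule, read from three places:

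- A1 lasts 1 or 2 weeks, by random allocation (Study Design and Procedures).
- B1 lasts 6 weeks (The TELE-BariACTIV Intervention). It therefore ends at study week 1 + 6 = 7 or 2 + 6 = 8.
- Around B1, accelerometry is scheduled in A1, mid-B1 and after B1 (Table 1).

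Only in study week 2 are some participants exposed while others are not, and no accelerometry is scheduled in the first week of B1. By mid-B1 everyone is exposed. No comparison of exposed and unexposed MVPA at the same study time is therefore available for the sizing estimate.

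To see the leverage, assume an observed change of 10 min/day and an SD of 15, so n = 15.70 × 225 / effect².

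- Intervention effect 10: 36 per arm.
- Effect 7.5 (75% of the change): 63 per arm.
- Effect 5 (50%): 142 per arm.
- Effect 12.5 (baseline raised by monitoring, so that the change understates the effect): 15.70 × 225/156.25 = 22.6, or 23 per arm.

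**The case against.** Much of the case on the other side stands, and it limits the point.

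- **A reader might infer that single-case effect sizes can never size a trial.** The article does not support that. The metric is unnamed and MVPA is defined in min/day. If raw differences are pooled, the heterogeneity and sampling variances together could give an SD of change, although imprecisely with 12 people. Leaving the metric to a fuller document is normal and is not the finding. The finding is the stated sufficiency.
- **A reader might take a parallel-group future trial as stated.** It is an inference. The article says only multicenter and large-scale.
- **A reader might think that Tau-U will be used for sizing.** It is a sensitivity analysis, placed after the sample-size sentence.
- **A reader might call the comparison uncontrolled and biased upward, leaving the next trial underpowered.** Neither is established. Baseline length is randomized, start dates differ, participants are their own controls, and interviews ask about life events. This control is weak, but it is not absent. Background says that "motivation and readiness for PA increased close to their surgical date", but that concerns motivation and readiness, not measured activity. Entry also requires surgery more than 12 weeks away. The activity watch is mailed before baseline and could raise A1, which would shrink the change.
- **All SDs are assumed.** This is correct, so the figures show possible error and not expected error.

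None of this makes a pooled effect alone sufficient. Nor does it make the control-group comparison hold for an estimate taken when everyone has been exposed.

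**Conclusion.** The point holds in limited form. The sufficiency claim in Statistical Analyses is too strong: without a named raw scale and a between-person SD, the pooled A1–B1 effect does not determine the size of a trial comparing people. If it is a within-person standardized difference, the resulting n per arm could be wrong by roughly 2- to 4-fold in either direction under the illustrative SDs. This rests on those assumed SDs and on the likely, but unstated, between-person design of the future trial.

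The control-group sentence in Principal Findings also needs qualifying. With baselines one week apart and everyone exposed by the end of B1, time trend, monitoring reactivity and regression to the mean are not separated from the intervention effect. Neither the size nor the direction of the net bias can be derived from the article.

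**What to change.** In Statistical Analyses:

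1. Define the individual effect for the first meta-analysis as the raw difference in mean MVPA (min/day) between A1 and the post-B1 window. Pool it by random effects and report it with a confidence interval.
2. From the same data, report the between-participant SD of post-B1 7-day mean MVPA, the between-participant SD of the change, and the pre-post correlation.
3. Keep Tau-U and its meta-analysis as a descriptive sensitivity analysis, not an input to sizing.
4. Replace the sufficiency sentence with wording such as: these estimates of within-person change and between-person variability are inputs to the later sample-size calculation, alongside its own design assumptions.

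In Principal Findings, qualify the control-group sentence: the A1–B1 estimate is a within-person change that is only weakly controlled for time effects.

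No new data, visits or participants are needed, because the planned accelerometry yields all of these quantities. The cost is a slightly more modest claim. Sizing the later trial on a target difference fixed in advance would be sensible, but that is advice for the later protocol and not part of this correction.

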## Methods

### Study Design and Procedures

The study uses a phased approach to behavior change intervention development supported by the Obesity Related Behavioral Intervention Trials model [31].

The study results will be reported according to the recommendations for single-case protocols in behavioral interventions [75]. Owing to the objectives of the study (feasibility, acceptability, and effect size exploration) and recommendations [31,76], this study is a multicenter study with a single-case experimental design with multiple base levels (ABAB’A). It is an open-label trial in which research staff, researchers, and participants are not blinded to the study objectives, intervention, and allocation, given the nature of the intervention and measures.

Approximately 2 weeks before the baseline assessment, the study will be explained by phone to potential participants and the selection criteria, checked. Eligible and interested participants will be sent an accelerometer and a A370 Polar (Polar Electro) watch with cables to recharge and information sheet by mail with a prepaid return envelope. Participants will be instructed to initiate the baseline assessment on the web (Limesurvey) once they receive their packages, including an informed consent form. Then, participants will be randomly allocated to a 1- or 2-week baseline A1 phase using a list of random numbers generated electronically by a person outside the project, and they will start the 5 phases of the study (A1-B1-A2-B2-A3; Figure 1). The A phases are observational phases without intervention, and the B phases are intervention phases with PA counseling delivered via Zoom technology platform. Participants had different dates of starting the study owing to the variability in their MBS dates. Phase A2 may also vary in length because the exact MBS date is usually not known when participants are to start the study.

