To meet the design standards that recommend at least 3 measurements per phase [75,77], MVPA is assessed continuously over 7 to 14 days during each phase. The storage limit of the accelerometer is 180 days, which ensures the feasibility of the measurement. Therefore, participants have to download the free Actisync application on a computer, connect the device with a cable, and then upload their anonymized accelerometry data using the Actigraph Centerpoint minimum every 180 days. Quality of life, anxiety and depressive symptoms, motivational regulations, basic psychological needs satisfaction and frustration, self-efficacy to overcome barriers to PA, PA enjoyment, and social support for exercise are assessed using a series of validated questionnaires 6 to 10 times via Limesurvey (Table 1). In addition, participants are asked to respond to questions regarding the acceptability of the protocol and intervention in web-based questionnaires before and after the intervention (phase B1), as well as during a web-based semistructured individual interview 1 to 4 weeks after phase B1. Medical records will be consulted at the end of the study with the participants’ authorization to validate the MBS date, medical conditions, and weight loss.

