	**Generalization measures (secondary outcomes for future large-scale trial)**			
		Health-related quality of life	RAND 36-item health survey	10; 1 to 3 days before phase A1, 1 to 3 days before, mid- and after phases B1 and B2, as well as 1, 6, and 12 months after MBS (phase A3)
		Anxiety and depressive symptoms	PHQ-9^c^ GAD-7^d^	10; 1 to 3 days before phase A1, 1 to 3 days before, mid- and after phases B1 and B2, as well as 1, 6, and 12 months after MBS (phase A3)
		Motivational regulations for PA^e^	BREQ2^f^	6; 1 to 3 days before and after each phase
		Basic psychological needs satisfaction and frustration	BPNSFS^g^	6; 1 to 3 days before and after each phase
		Self-efficacy for PA	Self-efficacity scale to overcome PA barriers developed by the study authors following Bandura’s recommendations	6; 1 to 3 days before and after each phase
		PA enjoyment	PACES^h^	6; 1 to 3 days before and after each phase
		Social support for exercise	SSES^i^	6; 1 to 3 days before and after each phase

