##### Generalization Measures (Secondary Outcomes for the Future Large-scale Trial)

As recommended in the study by Tate et al [75], generalization measures are administered to increase the external validity of the study [86]. Generalization measures are dependent variables measured in addition to the targeted behavior to assess whether the effects of the intervention will be generalized to other results in the scientific literature [87]. In this study, generalization measures are used to assess changes in several psychosocial factors related to PA, spanning SDT, SCT, and health.

Health-related quality of life is assessed using the generic *RAND*-36 questionnaire [88], a 36-item questionnaire evaluating 8 concepts: physical functioning, role limitations owing to physical health, role limitations owing to emotional problems, energy or fatigue, emotional well-being, social functioning, pain, and general health perceptions. In addition, the *RAND*-36 contains an additional item to assess the perceived change in health status. The overall physical and mental health scores will be calculated from the 8 subscales [88]. A 3- to 5-point increase in overall physical and mental health scores is considered clinically significant [89,90]. According to the literature, owing to the likely absence of weight loss associated with the pre-MBS intervention, a score of 3 will be used as the minimal clinically important difference (MCID) [28,91].

The severity of anxiety and depressive symptoms will be assessed using the Patient Health Questionnaire (PHQ-9) [92] and the Generalized Anxiety Disorder scale (GAD-7) [93] as recommended by Obesity Canada [8]. The PHQ-9 is a 9-item validated scale that assesses the intensity of depressive symptoms. The GAD-7 is a 7-item self-rating scale that assesses the severity of anxiety symptoms. The MCID for the PHQ-9 and GAD-7 [94], based on the range of baseline depressive or anxiety symptom severity, will be used. Then, the MCID range will be 0 to 10 points (10/21, 48%) on the GAD–7 and 0 to 14 points (14/27, 52%) on the PHQ-9 for participants with baseline very mild to high anxiety or depression symptoms [94].

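### Stability and range by phase cannot be judged for the five theoretical-construct scales, which are measured only at phase boundaries, and the PHQ-9/GAD-7 MCID range starts at 0 points

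*Protocol article*

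**What the plan says.** **Theoretical constructs.** The Statistical Analyses section groups PA enjoyment, motivational regulations, psychological needs, self-efficacy and social support with self-reported MVPA. It says that these measures "and self-reported MVPA will be analyzed using visual analysis", and that "stability, mean level change, and range of data by phase will be examined". Table 1 gives the schedule of each of the five construct scales as "6; 1 to 3 days before and after each phase". Study Design and Procedures sets out five phases in sequence, A1-B1-A2-B2-A3. The same section cites design standards that "recommend at least 3 measurements per phase", and uses them to justify the accelerometer schedule.

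**Self-reported MVPA.** In Table 1 the GPAQ has ten occasions, including the middle of B1 and of B2.

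**PHQ-9 and GAD-7.** The Generalization Measures section makes the MCID depend on baseline symptom severity and continues: "Then, the MCID range will be 0 to 10 points" on the GAD-7. The matching PHQ-9 range is 0 to 14. Statistical Analyses says that quality of life, anxiety and depression "will be analyzed using the Reliable Change Index or cutoff score for descriptive purposes".

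**The concern.** Stability and range describe how scores vary within a phase, so they need repeated observations inside it. A schedule placed only at phase edges does not provide them. The scales concerned measure the constructs that the intervention is built to change, and they are proposed as secondary outcomes for the large trial. If the visual analysis is reported as planned, a difference between two boundary scores will be presented as evidence about the level and stability of a phase, which it is not.

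The MCID point is separate. A minimal important difference of 0 is not a difference. Wherever it applies, it cannot tell a participant who changed from one who did not.

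**Working it through.** **1. Counting the construct assessments.** Inputs: 5 phases (Study Design and Procedures) and 6 assessments (Table 1).

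- Distinct boundaries of 5 consecutive phases: 5 + 1 = 6. This reproduces the stated 6, so every assessment is at a boundary.
- If before and after occasions were not shared there would be 2 × 5 = 10, which is not what Table 1 states.
- Interior assessments: 6 − 6 = 0.
- Shared assessments: A1/B1, B1/A2, A2/B2 and B2/A3, so 4 of the 6. Only the one before A1 and the one after A3 belong to a single phase.

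**2. What the planned summaries become.**

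| Assignment of boundary points | Points per phase | Range by phase | Stability |
|---|---|---|---|
| Shared by both neighbouring phases | 2 | absolute before-after difference | cannot be judged |
| Given to the phase just ended | 1 | 0 by construction | undefined |

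Under sharing, the means of neighbouring phases have one observation in common. Take B1, with x₁ before and x₂ after, and x₀ before A1. The A1 mean is (x₀ + x₁)/2 and the B1 mean is (x₁ + x₂)/2. Their difference is (x₂ − x₀)/2, in which x₁ cancels: it is half the change from before A1 to after B1. With one point per phase, the same comparison is x₂ − x₁. Either way, mean level change is a difference between two single scores.

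**3. For scale.** Three points in every phase would need 6 + 5 = 11 assessments with shared boundaries, or 3 × 5 = 15 without. The schedule has 6.

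**4. Self-reported MVPA.** Occasions: 1 (before A1) + 3 (B1) + 3 (B2) + 3 (1, 6 and 12 months) = 10, as stated. B2 starts 3 months after surgery, so by timing the 1-month occasion falls in A2. With shared boundaries this gives 2 points in A1 and 3 in each of B1, A2, B2 and A3. Check: 2 + 3 + 3 + 3 + 3 = 14, less 4 shared = 10. Only A1 lacks an interior point.

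**5. MCID range.** The stated percentages reproduce: 10/21 = 47.6% and 14/27 = 51.9%. Test whether zero change meets a threshold m, that is, whether 0 ≥ m. For m = 0 it does; for m = 1, 3 or 5 it does not. The fault is confined to the end of the range where the threshold is 0.

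**The case against.** Several objections have force.

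- **Not every questionnaire is affected.** A reader might infer that the visual analysis fails for everything it covers. It does not: self-reported MVPA has mid-phase points.
- **The three-measurement standard is cited for accelerometer MVPA, the target behaviour.** This stands. The construct scales breach no standard that the article sets for them. The point rests on promising stability and range by phase from a boundary-only schedule.
- **Mean and range can be computed from two points.** True, so the data are uninformative for this purpose rather than absent. Stability still cannot be judged.
- **Zero is the bottom of a severity-dependent range.** A reader might infer that unchanged participants generally will be classed as improved. The document does not support that. The zero applies only to the mildest baseline symptoms, Statistical Analyses names the Reliable Change Index or a cutoff without saying that the cutoff is the MCID, and the use is descriptive.
- **RAND-36.** A reader might also call the 3-point MCID an error because it lies within individual measurement error. With an assumed SD of 10 and reliability r of 0.85 to 0.95, the SD of change is 10√(2(1 − r)), or 5.5 to 3.2. Then 29% to 17% of truly unchanged people would gain 3 points or more, and the Reliable Change Index is 10.7 to 6.2. Neither input is in the document. An MCID concerns importance and the index concerns measurement error, so one may lie below the other without fault, and the index is already named for this outcome.
- **Index or cutoff.** Leaving that choice open is detail that an article may leave to the full protocol or analysis plan.

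What survives is the mismatch for the five construct scales and the zero at the low end of the PHQ-9/GAD-7 range.

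**Conclusion.** The point holds in this limited form and is minor. For the five construct scales there are 0 interior observations in any of the 5 phases and at most 2 at the edges, with 4 of the 6 assessments shared. Stability and range by phase cannot be assessed meaningfully, and mean level change is a before-after difference. This follows from the stated schedule and needs no outside assumption. The PHQ-9/GAD-7 MCID admits an unchanged score only where the threshold is 0, at the mildest baseline symptoms; the article does not show how many of the 12 participants that would be. Neither part touches the feasibility and acceptability objective, the six success criteria or the MVPA effect estimate.

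**What to change.** **Construct scales.** For BREQ-2, BPNSFS, self-efficacy, PACES and SSES, delete stability and range by phase. Report each participant's before-after change across each phase, descriptively or with the Reliable Change Index where a reliability is available. The article gives none for the self-efficacy scale written by the study team, so that scale may have to stay descriptive. Keep the visual analysis for self-reported MVPA.

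**PHQ-9 and GAD-7.** Do not count a change as important unless it is above 0 and exceeds the Reliable Change Index already named in Statistical Analyses. State that the MCID does not apply at minimal baseline symptoms.

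**Comparison with A1.** If the change from before A1 to before B1 is shown beside the B1 change, call it a limited comparison: A1 lasts 1 or 2 weeks and B1 six. Do not use it for B2, which follows surgery.

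**Cost.** Wording only, with no added assessments. Fewer participants will be labelled as changed.
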